### Participants and Recruitment Process

The study will enroll nursing students from a Portuguese Nursing School, and which are exposed to standing environments during acute clinical settings (e.g., hospitals). The recruitment process will be developed according to the following inclusion criteria: (i) nursing students enrolled, at the moment of the study, in a Nursing degree; (ii) nursing students that, at the moment of the recruitment phase, are not enrolled in a clinical learning setting; and the following exclusion criteria: (i) diagnosed chronic systematic diseases (e.g., rheumatoid arthritis); (ii) diagnosed metabolic disorders; (iii) visible lower limb swelling; (iv) presence of contraindications for baropodometric-related measurements; (v) history of orthopedic neurological and/or musculoskeletal problems likely to affect gait; and (vi) students that, at the moment of the recruitment phase, are also committed to a professional working activity or involved in high competition sports, which might influence foot health (e.g., waitress, door-to-door delivery, among others).

Participants will first be addressed in a project presentation session, where informed consent will be provided for their analysis and signature. Subsequently, the days for data collection will be scheduled, taking into consideration the most convenient periods for students and the research team. In this sense, a convenience sample will be recruited, as students will voluntary show up to participate in the study. This sampling method was chosen, rather than randomization, due to time constraints regarding project schedule, and also the need to achieve a representative sample. As we are performing the study only in one Nursing School, due to researchers' availability and ethical approvals, randomization could include students that wouldn't be able or didn't want to be part of the research in progress. In this sense, the research team opted to include volunteers, also helping decrease potential loss to follow-up.

In the Nursing School involved in this study, clinical training has an average duration of 4 to 5 months for students in the third and fourth year of the Nursing degree. Thus, the study will depend on this timeframe for the respective follow-up period.

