According to the defined criteria, all undergraduate nursing students at the third year will be recruited as participants. Each academic year, an average of 300 students are enrolled, and for a confidence interval of 95% and a margin of error of 5%, the sample size needed is 169 participants. Also, an a priori 0.05 significance level is defined and a response distribution of 50% is assumed. To prevent potential losses, we've added an additional 15% of the total sample size, thus aiming to recruit 194 students.

All data collection will take place inside the Nursing School, in specifically chosen places, previously tested for the study, and will be performed by two researchers, which will be different from those responsible to analyze data.

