### Exposures, Outcomes and Confounders

The exposure under study consists of a particular environment that poses particular biomechanical risks to the foot/ankle region. According to Bernardes et al. (15), standing environments include those of prolonged standing and prolonged walking, which can be defined as spending at least 5% of occupational time standing or walking (21).

The first primary outcome of interest is related to the change in podiatric profile at 5 months and will be evaluated at month 0 and month 5, being an objective and quantitative outcome. In this case, specific foot-related variables while walking will be recorded, illustrating the actual behavior of the foot during activity. The assessment of the podiatric profile follows the important premise that the medial longitudinal arch is one of the most important and highly variable structural characteristic of the human foot (22).

The relevant variables that describe this outcome are summarized in Table 1.

**Table 1 T1:** Specific podiatric profile variables.

**Category**	**Variables**	**Definition**
**Kinematic variables**	Forefoot width/spreading	Distance, in millimeters, between two straight lines perpendicular to the Chopart joint and tangential to most medial and most lateral points of the heads of first and fifth metatarsals, respectively.
	Foot angle at contact (sagittal plane)	Dorsiflexion angle at contact, in relation to the sagittal plane.
	Foot eversion	Or pronation, is an angular movement where the foot moves away from the medial plane.
	Foot adduction	Is the angular movement were the foot moves toward the medial plane.
	Foot external rotation	Rotation of the joint away from the midline, measured as an angle.
	Ankle inversion	Angular movement toward the medial plane.
	Medial longitudinal arch (MLA)	Located between the heel proximately and the medial three metatarsophalangeal joints anteriorly. Runs through metatarsals 1-3, sesamoid bones, cuneiform bones, navicular, talus, and calcaneus bones; the plantar aponeurosis, spring ligament, talocalcaneal ligament, and deltoid ligament; the flexor *hallucis longus*, flexor *digitorum longus, abductor hallucis*, flexor *digitorum brevis*, tibialis posterior.
	Ankle plantarflexion ROM in late stance	Refers to the angular distance of the movement around the ankle joint during the late stance of gait, characterized by a single limb support, and occurring before the swing period.

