### Study Layout

After recruitment, at month 0 (before exposure) and month 5 (after exposure), the participants will undergo a four-phased procedure:

Preparation: the trials will be explained to the participants and consent will be retrieved; any questions will be properly addressed;Familiarization: a test procedure will be performed where participants walk freely over the platform, without recording baropodometric gait analysis (BGA), to achieve the greatest possible freedom of movement. Participants will be asked to always walk barefoot.Trials: three types of gait protocols are usually applied in this type of study (one-step, two-step and mid-gait protocol). The choice should be based on both the variable of interest and the site of the foot to be studied. According to some authors (25, 26), there are few differences between the mid-gait (the *standard* protocol) and the two-step protocol, with similar values provided by both. An important criterion is using the same protocol throughout all studies, including follow-up.In this study, we chose to use the mid-gait protocol (Figure 1), particularly because the two-step termination protocol method is usually more appropriate for collecting joint kinematic data, which is out of the scope of this study, and also because the two-step initiation and termination protocols might delay acquiring the usual walking velocity during the trial (25, 26). In this sense, subjects will walk, at a self-selected pace, along an 8.0 m walkway. An initial position will be pre-established, to allow the right foot to hit the pedography platform at the middle of the walkway, with the fourth step, also avoiding gait alterations. After striking the platform, subjects will continue walking for 4.0 m until de end of the walkway.Additionally, participants will perform three valid trials per foot, as it has been previously found to be sufficient to ensure adequate reliability of force and pressure data (27–29) and will perform at least three steps before and after the pedography platform, as stated by Cousins et al. (27), that gait protocols should ideally involve a minimum preamble of at least three steps for a representative gait pattern to be obtained.It should be noted that a valid trial of a foot scan is defined as the participant hitting with the whole foot over the platform, without gait pattern alterations. A trial will be excluded, and should therefore be repeated, if a participant: (i) targets the borders of the platform with any part of the foot; (ii) alters gait to ensure full contact of the foot; and (iii) pauses on the mat.Self-Assessment of Foot Health: at the end of the BGA, participants will be asked to answer a self-assessment instrument about their current foot health, including skin, nail and presence of pain and will participate in a focus group together with another 5–10 participants from the study to discuss the influence of foot health in quality of life.

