### Statistical Analysis

The primary outcomes and the Foot Self-Care Knowledge (secondary outcome) will be analyzed using SPSS Statistics v25, namely with descriptive statistics (average; standard deviation; medians) with an *a priori* significance value of *p* < 0.05.

After verifying the type of distribution of the sample, using the Kolmogorov-Smirnov (KS) with Liliefors correction (suitable for samples with more than 30 subjects) (30), either the independent samples *t*-test (normal distribution) or the Mann-Whitney (test non-normal distribution) will be used to compare changes in outcomes before and after the exposure.

To relate variables of interest, namely podiatric profile variables and specific foot-health parameters, a Multiple Linear Regression will be computed and multivariate analysis of variance with repeated measures to detect significant interactions between variables.

To control confounding effects, we'll perform a stratification of variables, and evaluate the exposure-outcome association, also using Mantel-Haenszel (M-H) estimator for an adjusted result. Additionally, the Analysis of Covariance (ANCOVA) will be computed to assess the effect of certain factors on the outcome variables.

The secondary outcome, related to the students' perceptions, will be analyzed using ATLAS.ti v7 software, based on the content analysis as defined by Bardin (31). The different phases of analysis are: (i) pre-analysis; (ii) exploration of the material; and (iii) treatment of results, inference and interpretation. The categorical organization of the content will be performed *a posteriori*, through the following codification steps: (i) cutting—choice of units; (ii) enumeration—choice of counting rules; and (iii) classification and aggregation of chosen categories and units.

Potential missing data will be handled using marginal mean imputation, this is, computing the mean of the missing value, *X*, using the non-missing values and use it to impute missing values of *X*.

Regarding loss to follow-up, all data belonging to participants that choose to opt-out or are lost during the study, will be erased from storage, as explained in the informed consent document.

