## Discussion

We have described a protocol for a prospective observational cohort study, that aims to understand the influence of prolonged standing and walking positions on nursing students' foot health. This study will also explore the potential relationship between nursing students' podiatric profile and reported signs and symptoms.

Nursing practice is physically demanding, causing high loading forces, namely to the lower extremities. Additionally, common factors for increased risk for the development of foot/ankle disorders are footwear, constant standing and neglected foot care (6).

Currently, the study of injuries has been the subject of several studies, and some (31, 32) report that further investigations should be carried out into the circumstances and factors that cause problems at the level of foot/ankle region in this population.

Although several studies identify this problem, few describe in detail the causes of pain and discomfort. On the other hand, the podiatry evaluations conducted are poor (31), which limits a more detailed knowledge of the phenomenon under study. Moreover, and although some researchers suggest some solutions, namely the development of ergonomic and personalized footwear (33–35), there seems to be no adequate interventions to improve foot health in nursing students (4, 13).

Therefore, this study has the potential to comprehensively map significant foot/ankle changes caused by prolonged walking or standing positions, experienced by nursing students in clinical settings. Such data will be essential to establish a potential relationship between those factors. The conclusions will lead to a better understanding of the phenomena, thus allowing for better prevention. Additionally, the conclusions will lead to a better understanding of the phenomena, thus allowing for a better prevention, particularly through the development of guidelines and preventive tools.

Some limitations of the study are related to the convenience sample, which is recruited from a Nursing School in Portugal, reducing the external validity of the study. On the other hand, the follow-up time of 5 months, may be insufficient to elicit important signs and symptoms.

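### Exposure coincides with visit, so the Mantel-Haenszel exposure estimate has no between-student contrast and, read as before/after, measures change over time rather than the effect of standing or walking

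*Protocol article*

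**What the plan says.** All references are to the protocol article.

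- **Who is enrolled.** Participants and Recruitment Process describes students who are "exposed to standing environments during acute clinical settings (e.g., hospitals", and states that "all undergraduate nursing students at the third year will be recruited as participants". Students must not be in clinical training when recruited. Those with a job or in high-level sport at that point are excluded. No second group is described.
- **When exposure occurs.** Study Layout places the two assessments "at month 0 (before exposure) and month 5 (after exposure".
- **How exposure is defined.** Exposures, Outcomes and Confounders characterises it as an environment and gives one threshold, "spending at least 5% of occupational time standing or walking". It sets no hours or levels. Type of ward and type of nursing work appear as possible effect modifiers and confounders, not as the exposure.
- **What is recorded.** Table 2 lists the pressure platform, the two foot indices, the foot-health questionnaire, the foot-care knowledge test and focus groups. Instruments describes pressure, force, contact area and centre-of-pressure measures.
- **What is planned.** Confounding is to be handled by stratifying and by a step to "evaluate the exposure-outcome association, also using Mantel-Haenszel (M-H) estimator for an adjusted result", with ANCOVA in addition.
- **What is to be concluded.** The Discussion says the study could "comprehensively map significant foot/ankle changes caused by prolonged walking or standing positions". Its limitations are the convenience sample from one school and the short follow-up.

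**The concern.** An exposure-outcome association needs variation in exposure that can be told apart from other things. Here every student changes from unexposed to exposed between the same two visits, so exposure and calendar time move together. Nothing described grades students by how much they stood or walked, so there is no dose contrast to use instead.

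At stake is the stated aim, the influence of prolonged standing and walking on foot health. If the analysis returns only change over a training period, it cannot separate standing and walking from anything else that shifts over those five months, such as footwear, body weight, activity outside placement, or familiarity with the questionnaire and the gait protocol. A larger sample would not help. If exposure is not asked about by the month-5 visit, it will be hard to recover later. The Discussion intends guidelines and preventive tools to follow from the conclusions, so the causal wording has consequences.

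**Working it through.** **1. The plan's own figure.** The sample size is a precision calculation for one proportion with a finite-population correction (population 300, proportion 0.5, margin 0.05, 95% confidence).

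- n0 = z² p(1−p)/e² = 1.96² × 0.25 / 0.0025 ≈ 384.15 (z unrounded)
- n = 384.15 / (1 + 383.15/300) = 384.15 / 2.277 = 168.7, so 169
- 169 × 1.15 = 194.35, so 194

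Both figures reproduce. Neither involves an exposed/unexposed comparison, so the sample size gives no hint of which contrast the Mantel-Haenszel step should use.

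**2. Does the exposure threshold separate students?** The article gives no shift length, so I assume 8 to 12 hours. Five per cent is 0.05 × 480 = 24 minutes or 0.05 × 720 = 36 minutes. On a hospital ward, practically every student would exceed this, so the threshold classes the whole cohort as exposed.

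**3. Mantel-Haenszel between students.** In each stratum let a, b be exposed with and without the outcome, c, d unexposed with and without, and T the total.

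- OR = Σ(ad/T) / Σ(bc/T)
- RR = Σ[a(c+d)/T] / Σ[c(a+b)/T]

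With all students exposed, c = d = 0 in every stratum. Both ratios are 0/0, and the risk-difference weights Σ[(a+b)(c+d)/T] sum to 0. No estimate exists for any stratification or any sample size.

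**4. Mantel-Haenszel as month 5 against month 0, each student a stratum.** Here T = 2. Students with the same status at both visits contribute 0 to both sums. A student with the outcome only at month 5 adds 1 × 1/2 to the numerator, and one with it only at month 0 adds 1/2 to the denominator. Illustrative counts for 169 students (assumed, not from the article):

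| Outcome | Students |
|---|---|
| month 5 only | 30 |
| month 0 only | 12 |
| both visits | 40 |
| neither visit | 87 |

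OR = (30/2)/(12/2) = 15/6 = 2.5, which equals the matched-pair ratio 30/12. The estimate exists and controls fixed personal traits.

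**5. The choice of strata matters.** Pooling the same students without pairing gives 30 + 40 = 70 of 169 with the outcome at month 5 and 12 + 40 = 52 of 169 at month 0. Then OR = (70 × 117)/(99 × 52) = 8190/5148 = 1.59. This is a marginal rather than a within-person quantity, so 1.59 and 2.5 need not agree. The usual variance for the pooled version would also ignore the pairing. The article does not say which is meant.

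**6. What the before/after version estimates.** Write the outcome for student i at visit t as student effect + β × exposed + γ × (month 5). Exposed equals the month-5 indicator for everyone, so only β + γ can be estimated. Attributing the whole of it to standing and walking requires γ = 0, and the design offers no means of checking that.

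**The case against.** The strongest reply is that the article does state its contrast. Month 0 is deliberately unexposed person-time: students must be outside clinical training, and those with jobs or in high-level sport are excluded. The comparison is before against after, so the 0/0 result belongs to a between-student reading that the article never sets out. Mantel-Haenszel is also only one of several tools, alongside ANCOVA, regression and repeated-measures MANOVA, and the main before/after comparison does not depend on it. The causal phrase occurs in a hedged sentence of the Discussion, while both primary outcomes are framed as change.

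Much of this stands, and it limits the point in three ways.

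- A reader might infer that the Mantel-Haenszel estimate cannot be computed at all. The article does not support that: the person-stratified version in step 4 of the working is computable.
- A reader might infer that the strata would be wards and that each student's visits would wrongly be treated as independent. The article names no strata, so this is a possibility and not a stated error.
- A reader might infer that no exposure data will be collected. Table 2 is an outcomes table and Instruments covers the platform, so the article shows only that no such measure is described. A placement record may exist in fuller documents.

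The reply does not remove the confounding with time. The recruitment exclusions apply at recruitment and do not control what changes afterwards. ANCOVA and regression cannot supply an exposure contrast without an exposure variable, and none is named. Ward type could create a contrast, but it is designated a modifier or confounder and is given no standing or walking levels. The missing comparison is absent from the limitations.

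**Conclusion.** The point holds in this form. Exposure and visit are the same variable. The planned Mantel-Haenszel exposure-outcome estimate therefore has no between-student contrast (0/0 if all are exposed). As a matched before/after ratio it exists but estimates total change over five months. The causal statement in the Discussion goes further than either version can.

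There is no numerical bias to report, because its size depends on how much would have changed without the exposure, and the design does not observe that. The 24 to 36 minute range rests on assumed shift lengths. The ratios 2.5 and 1.59 rest on assumed counts and illustrate only how the choice of strata acts. The conclusion also assumes that no graded exposure record exists beyond those described. If one does exist, the remedy is to name it in the analysis.

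It would be going too far to say that the before/after analysis is worthless. Change over clinical training remains a legitimate, estimable quantity; what is not identified is the share due to standing and walking.

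**What to change.** 1. **Measure exposure.** At the existing month-5 visit, add short self-report items: usual hours per shift standing, usual hours per shift walking, number of shifts, and ward type. Cumulative exposure is hours per shift × number of shifts, kept separate for standing and walking where possible.
2. **Use it in the analysis.** Regress the month-5 outcome on cumulative exposure as a continuous variable, adjusting for the month-0 value, with ward type as a possible effect modifier. Use a logistic form for disorders recorded as present or absent. Do not use the 5% threshold to classify students.
3. **Resolve the Mantel-Haenszel step.** Either drop the exposed/unexposed analysis, or restrict it to a matched before/after contrast with each student as a stratum, and say so.
4. **Limit the claim.** Report the before/after result as change over clinical training, replace the causal wording in the Discussion, and add the lack of a concurrent less-exposed comparison to the limitations.

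The cost is a few questionnaire items at a visit that already takes place, plus changes of wording. The downsides are recall error in self-reported hours, imprecision if students' hours vary little, and a dose-response result that is still observational. If exposure cannot be collected, points 3 and 4 still apply, and the aim should be restated as describing within-student change.

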Another variable of interest to characterize the podiatric profile is plantar loading characteristics. As there is no current consensus in the literature for the definition of adequate foot segments, this study will consider the templates of similar studies, which showed good reliability for plantar forces and pressures during barefoot walking in healthy adults (23). Namely, the regions to assess and compare are: lateral heel, medial heel, midfoot, 1st metatarsophalangeal joint (1MPJ), 2nd−5th metatarsophalangeal joint (2–5MPJ), hallux and the lesser toes.

The second primary outcome concerns the change in foot health at 5 months, a subjective evaluation by the participant, and is related to observed clinical parameters, signs and symptoms, namely skin, nails, foot structure, as well as presence and location of the pain. The Portuguese adaptation of the Self-Administered Foot Health Assessment Instrument (S-FHAI), a Likert-type instrument with four dimensions, will be used. It will be applied at month 0 and month 5. The majority of observed foot disorders will be recorded as either present or absent.

The study also includes the following secondary outcomes: (i) Foot Self-Care Knowledge, which is assessed between month 0 and month 5, through a four-dimensional questionnaire, where specific interventions for the promotion and prevention of foot and ankle disorders are evaluated; and (ii) Students' perceptions about the influence of foot health in their quality of life. It is evaluated through focus groups after exposure time (month 5).

Regarding potential effect modifiers and confounders, we expect that different nursing activities and ward typology (e.g., surgical units, intensive care) might produce diverse baropodometric patterns.

The primary and secondary outcomes, respective instruments for evaluation and timeframes for assessment are summarized in Table 2.

**Table 2 T2:** Primary and secondary outcomes assessment.

			**Assessment**	**Timeframe**		
				**Month 0**	**Month 3**	**Month 5**
**Primary Outcomes**	Change in Podiatric Profile at 5 months^*^	Kinematic variables	EMED® software	x		x
		Kenetic variables		x		x
		Foot posture	MAI analysis	x		x
		Foot function	CPEI analysis	x		x
	Change in Foot Health at 5 months	Skin health	Portuguese adaptation of the self-administered foot health assessment instrument [S-FHAI; (24)].	x		x
		Nail health		x		x
		Foot structure		x		x
		Foot pain		x		x

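### Ward-related factors would be tested as if students were independent; if students share wards, standard errors for those factors are too small

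*Protocol article*

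**What the plan says.** Under Exposures, Outcomes and Confounders, ward type and nursing activity are put forward as potential effect modifiers and confounders: "we expect that different nursing activities and ward typology (e.g., surgical units, intensive care) might produce diverse baropodometric patterns".

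The Statistical Analysis section then commits to specific methods:

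- For the before/after comparison, an independent-samples t-test or Mann-Whitney test "will be used to compare changes in outcomes before and after the exposure".
- For associations, "a Multiple Linear Regression will be computed and multivariate analysis of variance with repeated measures to detect significant interactions between variables".
- For confounding, "To control confounding effects, we'll perform a stratification of variables, and evaluate the exposure-outcome association, also using Mantel-Haenszel (M-H) estimator".
- For factor effects, "Additionally, the Analysis of Covariance (ANCOVA) will be computed to assess the effect of certain factors on the outcome variables".

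Neither the strata nor the ANCOVA factors are named. No method is described with a ward term that allows for correlation between students, or with a cluster-robust variance. Under Participants and Recruitment Process, third-year students of one school are recruited, from about 300 enrolled per year, with clinical training averaging 4 to 5 months in acute settings. The article does not say how many wards are used, how many students share one, how students are allocated, or whether they rotate.

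**The concern.** Ward type is a property of the ward, not of the student. When several students train on the same ward, they share its value of the factor. They probably also share conditions that affect the foot outcomes, so their results are likely to be positively correlated. An ANCOVA or regression on individual students then counts each ward several times when it estimates a ward-type effect. The precision of that effect depends largely on the number of wards, not on the number of students alone.

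At stake are the factors that the plan itself singles out. Understated standard errors would make differences between ward types look firmer than they are, with a false-positive rate above the stated 0.05. The Discussion intends the conclusions to feed guidelines and preventive tools, so a spurious ward finding could be carried forward.

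**Working it through.** **The plan's own figure.** Inputs from Participants and Recruitment Process: population 300, 95% confidence, 5% margin, 50% response distribution.

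- n0 = 1.96² × 0.25 / 0.05² = 384.16
- n = 300 × 384.16 / (384.16 + 299) = 168.70, so 169
- 169 × 1.15 = 194.35, so 194

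Both stated figures reproduce. Neither contains an allowance for clustering.

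**Effect of shared wards on a ward-level factor.** Students per ward (m) and the intra-ward correlation (ICC) are not in the document, so both are assumed. The formulas also assume equal ward sizes, exchangeable correlation, a two-sided test and a normal approximation.

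- Design effect: DE = 1 + (m − 1) × ICC
- True SE / naive SE = sqrt(DE)
- Actual error at nominal 5% = 2 × (1 − Φ(1.96 / sqrt(DE)))
- Effective n = 169 / DE

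| m | ICC | DE | SE factor | Actual error | Effective n of 169 |
|---|---|---|---|---|---|
| 3 | 0.02 | 1.04 | 1.02 | 5.5% | 162 |
| 3 | 0.10 | 1.20 | 1.10 | 7.4% | 141 |
| 5 | 0.05 | 1.20 | 1.10 | 7.4% | 141 |
| 5 | 0.10 | 1.40 | 1.18 | 9.8% | 121 |
| 10 | 0.05 | 1.45 | 1.20 | 10.4% | 117 |
| 10 | 0.10 | 1.90 | 1.38 | 15.5% | 89 |

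**Do the planned adjustments absorb it?** A fixed ward-type factor, or strata by ward type, removes mean differences between types. Two students on the same surgical ward can still be more alike than two students on different surgical wards. That residual correlation is the ICC in the formula, and neither ANCOVA nor Mantel-Haenszel as named addresses it. Repeated-measures MANOVA models correlation within a student, not between students.

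**The before/after test.** The named test is for independent samples, but it is applied to the same students at month 0 and month 5. With rho the correlation between the two measurements in a student, and equal variances at both times:

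- True SE / naive SE = sqrt((1 − rho) × DE)
- The interval is too narrow only if DE > 1 / (1 − rho), that is 1.43 at rho = 0.3, 2.0 at rho = 0.5 and 3.33 at rho = 0.7.

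At the largest DE in the table, 1.90, this requires rho below 1 − 1/1.90 = 0.47. At rho = 0.5 the ratio is sqrt(0.5 × 1.90) = 0.975, so the interval is slightly too wide.

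**The case against.** The strongest objection is that ward sharing is nowhere stated. The article gives no ward count, no allocation method and no sign that a student stays on one ward. That is correct, so the point must be conditional. The condition is nevertheless very likely to be met: without sharing, 169 to 194 students in one school year would need as many separate wards.

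Second, the article speaks of ward typology, which the planned stratification and ANCOVA could handle. This holds for differences between types only. It also means that the article supplies no evidence on the size of the correlation within individual wards.

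Third, a reader might infer that all intervals in the study are too narrow, including those for the mean change. The document does not support that. The before/after test as written ignores pairing, which widens its interval and can outweigh clustering. A reader might also infer that stated comparisons between wards are overstated, but the plan defines none and leaves its ANCOVA factors unnamed. Testing ward type there is the natural reading of the two sections together, not a written contrast.

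Fourth, a condensed article may leave covariance detail to a fuller plan. That lowers confidence. It does not remove the point, because the article names its methods and, as named, they do not fit a ward-level factor.

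Finally, the magnitude rests on assumed m and ICC, and at the low end it is small. The 169 is sized for estimating a proportion, so the effective-n column only illustrates lost information and is not a power statement.

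**Conclusion.** The point holds for ward type and other ward-level factors, on the condition that students share wards. Their standard errors would then be understated by a factor of 1.02 to 1.38, with an actual error of about 5.5% to 15.5% at nominal 5%, over the assumed m of 3 to 10 and ICC of 0.02 to 0.10. For nursing activities or other covariates that vary between students on the same ward, the understatement is smaller than the full design effect. Once the mean change is analysed as paired, the same inflation would apply to it; for the test as written, the direction is not fixed. The change is worth making, with medium confidence, since the size depends on two quantities that the document does not give.

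**What to change.** Record the placement unit or units of each student, and name the ward and activity factors to be analysed. In the analyses of ward-type or activity effects, add a random ward intercept or use cluster-robust standard errors by ward with a small-sample correction. Do the same for the mean change once it is analysed as paired. If students rotate through several wards, assign the main unit or use a multiple-membership term.

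The cost is one identifier per student, best collected while placements are running, and a standard mixed model. Intervals will be somewhat wider. If wards are few, or hold only one or two students each, the ward variance will be imprecisely estimated, and the report should say so.
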